## Abstract

**Materials and methods:**

This protocol was developed according to the guidelines of the Standard Protocol Items: Recommendations for Interventional Trials 2013 Statement (SPIRIT) and presents a randomized clinical trial with women who are dissatisfied with their bodies and live in southern Brazil. Participants will be randomized to the self-compassion or diet group and attend eight-week weekly meetings. Body image dissatisfaction will be assessed using the Body Shape Questionnaire (BSQ), dysfunctional eating will be assessed using the Three Factor Eating Questionnaire (TFEQ-RS21), and levels of self-compassion will be measured using the Self-Compassion Scale (SCS). The participants will answer the tools at the beginning of the study, at the end of the 8-week intervention, and 3 and 6 months after the end of the meetings.

**Discussion:**

This will be the first study to compare these two approaches using body dissatisfaction and eating behavior as outcomes, not just body weight. To date, only observational studies have evaluated the relationship between self-compassion, body dissatisfaction, and dysfunctional eating behavior.

**Trial Registration:** ClinicalTrials.gov NCT06084260

## Introduction

Sociocultural factors greatly influence the female body, so to be considered beautiful, it must be slim, with a greater degree of muscle definition and as little fat as possible [1,2]. This standard of beauty has contributed to an increase in body dissatisfaction and low self-esteem in women [3,4]. Dissatisfaction with the body seems to be starting earlier and earlier, being present as early as childhood, and is more prevalent in women than in men [5–7].

Body dissatisfaction is a risk factor for the incessant search for the ideal body, dysfunctional eating behavior [8], as well as the practice of energy-restricted diets [9,10]. Weight loss programs and energy-restricted diets have been practiced for several years [11,12] to deal with body dissatisfaction. Although they show results in the short and medium term, such programs are ineffective in maintaining weight in the long term [11,12] and can contribute to weight regain [13]. In addition, these programs are considered harmful because they favor dysfunctional behaviors’ development involving cognitive restriction, binge eating, uncontrollable desire for food, worry, and guilt when eating [14]. Furthermore, such diets, together with the fear of gaining weight and exaggerated preoccupation with food, calories and physical appearance, can be related to a failure’s sense, lack of control over one’s own life, decreased self-esteem, guilt, irritability, anxiety, depression [12] and the incidence of eating disorders [15–17].

In recent years, approaches have emerged that aim to promote healthy eating behavior without focusing on losing body weight [18] as an alternative to weight loss programs based on food restriction. Interventions without the use of diets have shown psychological benefits, such as an improvement in general psychological well-being and a reduction in suffering, weight-related stigma and body dissatisfaction [19,20], as well as greater eating competence, intuitive eating [21], a reduction in cognitive restriction and lack of eating control, and long-term weight loss [18].

One of these approaches is self-compassion, a theory derived from Buddhism that has shown a positive association with better mental behavior and health parameters [22]. It is a practice that can be learned, accessible anytime, and may relieve suffering [23]. Being self-compassionate implies being moved by one’s own suffering and treating oneself with care and empathy [24]. Individuals with worse mental health tend to have less self-compassion [25] while being more self-compassionate tends to reduce psychopathology [26] and help with emotional regulation [27]. In this sense, one study showed a relationship between a higher self-compassion level and a reduction in negative thoughts related to the body [28], a reduction in eating psychopathology and concerns about body image, which may be an adaptive emotional regulation strategy in eating disorders and body dissatisfaction [29].

Other studies have also shown that self-compassionate individuals seem to worry less about their body weight and are less ashamed of their bodies, as well as having a greater self-image valuing and appreciation [29–31]. However, no intervention studies in the literature evaluate the effectiveness of an approach based on self-compassion techniques focused on food compared to the traditional approach with an energy-restricted diet and its impacts on body dissatisfaction. For this reason, the study’s main objective is to compare the effect of a nutritional approach using self-compassion techniques with the traditional diet method over eight weeks on body image dissatisfaction and eating behavior in women dissatisfied with their weight.

## Materials and methods

This study protocol for a randomized clinical trial was developed under the guidelines proposed by the Standard Protocol Items: Recommendations for Interventional Trials 2013 Statement (SPIRIT) (S1 Table) [32]. Fig 1 shows the recruitment, intervention, and evaluation schedule.

**Fig 1 pone.0324030.g001:**
[figure not shown]
Schedule of recruitment, intervention and evaluation.

### Participants, study setting, and eligibility criteria

The study will be conducted with Brazilian women experiencing weight-related body dissatisfaction. To be included in the study, participants must present body dissatisfaction, be between 25 and 50 years old, have access to a cell phone with communication apps (WhatsApp), and be available to attend face-to-face meetings once a week for eight weeks. Participants will be excluded from the study if they have a diagnosis of depression, mood disorders (anxiety, bipolar disorder, borderline), eating disorders, or a history of suicidal ideation; if they have chronic diseases such as diabetes, kidney disease, cardiovascular and/or neurological diseases; and if they are pregnant or have been pregnant for six months or less; and to conclude, if they are menopausal.

### Recruitment

Recruitment will take place from March 4, 2024, to March 31, 2026, which is the estimated timeframe to achieve the calculated sample size. Participants will be recruited through posts on the researchers’ social networks, and those who express an interest will be contacted for an initial conversation via WhatsApp video call. This assessment will confirm the participant’s desire to participate in the study, the inclusion and exclusion criteria, and guidance on the study protocol. After confirming eligibility and signing the Informed Consent Form, the participants will be randomized and assigned to one of the two intervention groups: self-compassion or diet. The groups will take place weekly through face-to-face meetings, which will take place over eight weeks and will be one hour long. The group will be led by nutritionists previously trained in the two approaches. The adherence rate will be controlled, requiring a minimum participation of 75% (6 meetings) to be maintained in the entire study (baseline to eight weeks, three and six months follow-up).

Before the first meeting, all participants will answer an anamnesis and three validated scales for assessing eating behavior and body dissatisfaction, which will be available through the *Google Forms* platform. The same scales will be answered after the eight meetings (the end of the group), three months after the last meeting, and six months after the last meeting. Fig 2 shows the study flow diagram.

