### Interventions

Self-Compassion Group: the group with a self-compassion approach will have its own protocol created for the study. This intervention was based on self-compassion exercises proposed in “The mindful self-compassion workbook: a proven way to accept yourself, build inner strength, and thrive” [33]. Table 1 shows the topics covered in each meeting.

**Table 1 pone.0324030.t001:** Description of the meetings in the Self-Compassion group.

Meeting	Central theme	Dynamics
Meeting 1: How have I dealt with myself when it comes to my body and food?	Presentation and measurement of anthropometric measurements (weight and height) Self-criticism	Reflection on self-criticism
Meeting 2: Changing my relationship with my body through self-compassion“	Self-compassion and self-kindness	How do I treat a friend? Mindfulness exercise (Gabi Damasceno) adapted
Meeting 3: Where does it all come from? Looking at my history with food and my body	Mindfulness	What would you change about your body“video Accepting our bodies with self-compassion
Meeting 4: Shared humanity in body dissatisfaction and food: is it just me?	Shared humanity	Reflection exercise on shared humanity
Meeting 5: Mindful eating: the power of observation	Mindful eating	Mindful eating exercise
Meeting 6: Changing my eating habits in a compassionate way	Self-compassion as a tool for changing habits	Changing in a self-critical way vs. a self-compassionate way Dynamics in pairs
Meeting 7: Changing the way how I look at my body	Mindfulness Self-kindness	Mindfulness exercise (describing vs. judging) Self-compassionate letter to the body 100th birthday party“exercise
Meeting 8: Cultivating self-compassion in my life - what I’ve changed in how I look at my food and body.	Resumption of all previous subjects	My Mad Fat Diary“video scene Dynamics in pairs Closing

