### Sample size

Considering the study by Albertson, Neff and Dill-Shackleford (2014) [40], which found an improvement in body dissatisfaction from meditation based on self-compassion techniques with an effect size of 0.73 (high), a sample size of 76 people (38 for each group) was calculated. This calculation considered a power of 80%, a significance level of 5% and a Cohen’s d of 0.7 to test whether there is a minimal difference in the body dissatisfaction averages and self-compassion levels between the intervention and control groups, already including an addition of 10% for possible losses and refusals.

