### Statistical analysis

Baseline characteristics of the participants will be compared between groups (self-compassion and diet). For categorical variables, the Pearson Chi-square test will be used, with continuity correction for dichotomous variables or Fisher’s exact test when at least one cell has an expected count of less than five. For continuous numerical variables, the Shapiro-Wilk test will assess normality. If normality is accepted, results will be presented as mean and standard deviation and analyzed using Student’s t-test for independent samples. If the distribution is non-parametric, data will be expressed as median and interquartile range and analyzed using the Mann-Whitney U test. No significant differences between groups at baseline are expected due to the randomization process, which should provide similar groups. However, if significant differences are observed, these variables will be included as adjustments in multivariable analyses, as described below for primary and secondary outcomes.

Comparisons between baseline and follow-up for the primary and secondary outcomes will be tested using a General Linear Model (GLM) for repeated measures, considering the interaction between group (self-compassion and diet) and time (before and after). Separate analyses will be conducted for each follow-up point: from baseline to the end of the 8-week intervention, from baseline to 3 months after the intervention, and from baseline to 6 months after the intervention. Differences will be considered statistically significant at p < 0.05. The data will be analyzed using Statistical Package for the Social Sciences (SPSS) software, version 26.0.

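### Both arms are treated in meeting groups, but the sample size and the repeated-measures model assume independent women; if outcomes correlate within groups, the main test rejects too often and the 80% power carries no allowance for it

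*Protocol article*

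**What the plan says.** **Delivery.** Women are randomised individually, 1:1 (Randomization, allocation and masking of groups). Both arms are then treated together: "The groups will take place weekly through face-to-face meetings, which will take place over eight weeks and will be one hour long" (Recruitment). Nutritionists trained in both approaches lead the meetings. Day, time and place are fixed (Adherence, modifications, and concomitant care). Some content is interactive by design, for example "Reflection exercise on shared humanity" and work in pairs in the self-compassion arm (Interventions, Table 1). The exception is week 5 of the diet arm, which is an individual online consultation (Interventions, Table 2).

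**Sample size.** "This calculation considered a power of 80%, a significance level of 5% and a Cohen’s d of 0.7", and "a sample size of 76 people (38 for each group) was calculated", with 10% for losses already included (Sample size).

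**Analysis.** A repeated-measures general linear model is fitted separately for baseline to each follow-up, "considering the interaction between group (self-compassion and diet) and time (before and after" (Statistical analysis). Group here means treatment arm. "Differences will be considered statistically significant at p < 0.05".

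The text gives no size or number of meeting groups, no intraclass correlation, no design effect and no model term for meeting group.

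**The concern.** Women who spend eight weeks in the same meeting group share its dynamics and its calendar period, so their outcomes after treatment may be more alike than those of women from different groups. Each woman then carries less independent information than the calculation assumes. The planned standard error for the arm comparison would be too small, the p-value too low and the interval too narrow. Chance differences between a few meeting groups could then be read as a difference between the two approaches. This bears on the trial's main conclusion, because the group-by-time test at 5% decides which approach is declared better.

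The point cannot be set aside as detail for an analysis plan that is not shown. The article itself fixes the N, the power and the model.

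**Working it through.** **1. Reproduce the plan's N.** Inputs from Sample size: d = 0.7, power 80%, alpha 5%, 10% losses. Two-sided testing is assumed because sidedness is not stated. A two-sample t-test on independent observations (noncentral t) needs 34 per arm. Then 34 / 0.9 = 37.8, rounded up to 38 per arm, or 76 in total. The match is exact, so 76 contains no allowance for clustering.

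**2. Effect of clustering on a follow-up-only comparison.** Group size m and ICC are assumptions.

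- Design effect: DE = 1 + (m − 1) × ICC
- Effective n per arm: n / DE
- Factor by which the true standard error exceeds the naive one: √DE
- True type I error of the naive 5% test: 2 × [1 − Φ(1.96 / √DE)]
- Power: noncentral t at d = 0.7 with the effective n and 2 × (effective n) − 2 degrees of freedom

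For m = 10:

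| ICC | DE | Effective n (of 34) | SE factor | Type I error | Power, 34 per arm | Power, 38 per arm |
|---|---|---|---|---|---|---|
| 0 | 1.00 | 34.0 | 1.00 | 5.0% | 81% | 85% |
| 0.01 | 1.09 | 31.2 | 1.04 | 6.0% | 78% | 82% |
| 0.05 | 1.45 | 23.4 | 1.20 | 10.4% | 65% | 70% |

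Worked line: 1 + 9 × 0.05 = 1.45; 34 / 1.45 = 23.4; 1.96 / 1.204 = 1.63, giving a two-sided 10.4%.

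For m from 8 to 12, DE runs from 1.07 to 1.11 at ICC 0.01 and from 1.35 to 1.55 at ICC 0.05. Type I error runs from 5.8% to 6.3% and from 9.2% to 11.5%.

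**3. Few groups.** A correct analysis has degrees of freedom set by the number of meeting groups. With 34 women in groups of 10 there are 3.4 groups per arm, so about 2 × 3.4 − 2 = 4.8 degrees of freedom. Power falls to about 60% at ICC 0.01 and 48% at ICC 0.05.

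**4. The planned change analysis.** The group-by-time contrast between two visits is a comparison of change scores. Meeting groups can act only after baseline, so the cluster variance enters the follow-up score alone. Let ρ be the correlation of baseline with follow-up, with unit variance at each visit and d = 0.7 in those units. The change variance per woman is 2(1 − ρ). With clustering, the variance of an arm mean is [2(1 − ρ) + (m − 1) × ICC] / n. The ratio of the two, R, replaces DE in the type I error formula and in the degrees of freedom. For m = 10 and 34 per arm:

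| ρ | R, ICC 0.01 | Type I | Power | R, ICC 0.05 | Type I | Power |
|---|---|---|---|---|---|---|
| 0.5 | 1.09 | 6.0% | 78% | 1.45 | 10.4% | 65% |
| 0.6 | 1.11 | 6.3% | 85% | 1.56 | 11.7% | 71% |
| 0.7 | 1.15 | 6.8% | 93% | 1.75 | 13.8% | 78% |

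The power columns are for a test with the correct standard error. A simulation of the naive change-score test under no arm difference (4 groups of 9 per arm, ρ = 0.6, 20,000 runs) rejected 6.2% of the time at ICC 0.01 and 10.9% at ICC 0.05.

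**5. Which model term helps.** Write the scores of woman i in meeting group j as y0 = b_j + … and y1 = b_j + c_j + …, where c_j is what the meetings add. A random intercept for meeting group models b_j, which cancels in y1 − y0. The term that inflates the variance is c_j. In models fitted to simulated data, adding only the intercept left the group-by-time standard error essentially unchanged (0.230 against 0.230 in one data set). A baseline-adjusted follow-up model with a meeting-group random effect widened it.

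**The case against.** **Every input to the size is assumed.** The article gives no ICC, group size or number of groups. At ICC 0 nothing is wrong, and at ICC 0.01 the inflation is slight. This stands, so the point is conditional. A reader might infer that the standard errors are too small and the trial underpowered as a matter of fact. The document does not establish that.

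**The planned test may have power in reserve.** A change analysis gains when ρ exceeds 0.5: at ICC 0.01 power is 85% with ρ = 0.6. With no losses, even the follow-up-only figure at ICC 0.01 is 82%. This also stands for power. It does not rescue the type I error, which rises with ρ in the table above.

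**Clustering may be weak or unequal.** Meeting content is fixed, diet plans are individual, one diet session is individual and online, and pair work is listed only for the self-compassion arm. These features could lower the ICC, especially in the diet arm. They do not show that it is zero.

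**Leader effects.** A reader might infer that leaders confound the comparison. The document does not support this: the nutritionists are trained in both approaches and may lead groups in both arms.

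**Several groups per arm is an inference** from recruitment over about two years. If each arm had one group, arm and meeting group could not be separated at all.

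**Conclusion.** The point holds in conditional form. The N and the model both assume independent women, although treatment is delivered in groups in both arms apart from the diet arm's week 5. Any positive within-group correlation after treatment makes the group-by-time test anti-conservative. With about 10 women per group, the type I error would be about 6% at ICC 0.01 and about 10% at ICC 0.05, and somewhat higher for the change analysis if ρ exceeds 0.5. Follow-up-only power with 34 evaluable per arm would be about 78% and 65% (82% and 70% with 38), and lower with cluster degrees of freedom. Whether the planned change analysis falls short of 80% depends on both the ICC and ρ, neither of which is given. The direction is certain for any positive ICC; the size is not.

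**What to change.** 1. Record a meeting-group ID for every participant, now, while it is easy to do.
2. In Statistical analysis, model each follow-up score adjusted for its baseline value, with a random effect for meeting group and Satterthwaite or Kenward-Roger degrees of freedom. If the repeated-measures form is kept, include a meeting-group-by-time random effect. A meeting-group random intercept alone is not enough, because it cancels out of the group-by-time contrast.
3. In Sample size, state that the 80% power assumes no within-group correlation, and give power for ICC 0.01 and 0.05 at the actual meeting-group size.
4. Keep N at 76.

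The cost is one extra variable, one model term, wider intervals and a less favourable stated power. No extra participants are needed and nothing in the interventions changes.

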**Fig 2 pone.0324030.g002:**
[figure not shown]
Flow diagram.

### Interventions

Self-Compassion Group: the group with a self-compassion approach will have its own protocol created for the study. This intervention was based on self-compassion exercises proposed in “The mindful self-compassion workbook: a proven way to accept yourself, build inner strength, and thrive” [33]. Table 1 shows the topics covered in each meeting.

**Table 1 pone.0324030.t001:** Description of the meetings in the Self-Compassion group.

Meeting	Central theme	Dynamics
Meeting 1: How have I dealt with myself when it comes to my body and food?	Presentation and measurement of anthropometric measurements (weight and height) Self-criticism	Reflection on self-criticism
Meeting 2: Changing my relationship with my body through self-compassion“	Self-compassion and self-kindness	How do I treat a friend? Mindfulness exercise (Gabi Damasceno) adapted
Meeting 3: Where does it all come from? Looking at my history with food and my body	Mindfulness	What would you change about your body“video Accepting our bodies with self-compassion
Meeting 4: Shared humanity in body dissatisfaction and food: is it just me?	Shared humanity	Reflection exercise on shared humanity
Meeting 5: Mindful eating: the power of observation	Mindful eating	Mindful eating exercise
Meeting 6: Changing my eating habits in a compassionate way	Self-compassion as a tool for changing habits	Changing in a self-critical way vs. a self-compassionate way Dynamics in pairs
Meeting 7: Changing the way how I look at my body	Mindfulness Self-kindness	Mindfulness exercise (describing vs. judging) Self-compassionate letter to the body 100th birthday party“exercise
Meeting 8: Cultivating self-compassion in my life - what I’ve changed in how I look at my food and body.	Resumption of all previous subjects	My Mad Fat Diary“video scene Dynamics in pairs Closing

Diet group: in the diet group, participants will complete a 24-hour food recall (24HR). They will receive a food plan calculated by a nutritionist using the Estimated Energy Requirement calculation [34] as a reference and adjusted to their routine based on the 24HR. The necessary nutritional adjustments will be made to ensure adequate fiber, macro, and micronutrient intake according to the Dietary Reference Intakes [35] for women. The total energy value will depend on the participant’s goal, with a calorie deficit of 300 kcal for those wishing to lose weight and a surplus of between 300–500 kcal for those wishing to gain weight. The macronutrient distribution will be the AMDR of 45–65% carbohydrates, 10–35% proteins, and 20–35% lipids. Table 2 shows the topics covered at each meeting. In the fifth week of the study, the participants will have an individual online consultation to re-evaluate the proposed diet and adjust it if necessary instead of a group meeting.

**Table 2 pone.0324030.t002:** Description of meetings in the Diet group.

Meeting	Central theme	Dynamics
Meeting 1: Presentation and performance of anthropometric measurements	Presentation and measurement of anthropometric measurements (weight and height) Application of anamnesis to calculate the diet plan	Conversation about the purpose of the group and the participants
Meeting 2: Motivation for weight loss	Consequences of being overweight and sedentary and the importance of cultivating healthy lifestyle habits	Written reflection
Meeting 3: How to choose food?	Classification of foods according to the Food Guide for the Brazilian population (2014)	Food classification dynamics
Meeting 4: How to read food labels?	Reading food labels	“Which food is healthier” dynamic
Meeting 5: Guidance and monitoring of the diet plan	Food plan	Individual guidance on the diet plan (online)
Meeting 6: Myths and truths about healthy eating	Demystifying beliefs about healthy eating	Dynamics of myths and truths
Meeting 7: How to use carbohydrates to my advantage	Glycemic index and glycemic load Smart food combinations	High-fiber foods vs. low-fiber foods
Meeting 8: Cultivating healthy habits in my life	Ways to cultivate healthy habits in the long term	Clarification of doubts Closing

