### Data management

The data will be collected by two independent authors and stored in an SPSS® file database. The tools used to obtain the outcomes will be evaluated at the beginning (week 0) and after the intervention (week 8) and again at three and six months *follow-up*. All forms will be made available via *Google Forms.*

One of the researchers will send a WhatsApp message every week to promote participant retention and complete follow-up, encouraging participants to come to the meetings. Also, the messages sent will be the same for both groups and will include reminders about the meeting days, location, time, and any materials participants may need to bring for the activities. To those who discontinue or deviate from the intervention protocol, all data exclusion will be necessary.

The data collected will be saved on an institutional drive linked to the researcher in charge and shared only with the other researchers in the study. The data are expected to be stored for two and a half years (until the end of 2025), following the study schedule.

An interim analysis could be conducted if preliminary results need to be presented at scientific events relevant to the institutions involved in the study’s development. However, if such analyses could compromise the reliability of the data, they will not be performed*.* All authors could have access to interim results, but only the study coordinator ([name]) could decide to terminate the trial.

The plans for investigators and sponsor to communicate trial results are: a) Individual disclosure of the basal and post-intervention results to each participant; b) A public seminar with grouped results at sponsor institution to healthcare professionals; c) Public disclosure in scientific events, preprint, and scientific article publication.

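### The diet arm's 300 kcal deficit follows the participant's wish alone, so as written an underweight woman who wishes to lose weight would be prescribed a deficit

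*Protocol article*

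**What the plan says.** The Interventions section of the protocol article describes the diet arm. A nutritionist calculates each food plan with the Estimated Energy Requirement as reference and fits it to the woman's routine. The total energy is then set by her goal: "The total energy value will depend on the participant’s goal, with a calorie deficit of 300 kcal for those wishing to lose weight". The opposite goal has its own provision in the same sentence: "a surplus of between 300–500 kcal for those wishing to gain weight". Nutrient content is also covered: "The necessary nutritional adjustments will be made to ensure adequate fiber, macro, and micronutrient intake".

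Table 2 lists for meeting 1: "Presentation and measurement of anthropometric measurements (weight and height) Application of anamnesis to calculate the diet plan". In the fifth week there is an "individual online consultation to re-evaluate the proposed diet and adjust it if necessary instead of a group meeting".

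The eligibility section requires body dissatisfaction, age 25 to 50, a phone with WhatsApp and availability for weekly meetings. Its exclusions begin: "Participants will be excluded from the study if they have a diagnosis of depression, mood disorders (anxiety, bipolar disorder, borderline), eating disorders". They go on to a history of suicidal ideation, chronic diseases, current or recent pregnancy, and menopause. Neither list mentions weight or body mass index (BMI).

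**The concern.** The trial recruits on dissatisfaction with the body, not on excess weight. The surplus for women who wish to gain weight shows that the sponsor did not expect everyone to be overweight. A thin woman who is unhappy with her body and wants to be thinner is therefore a foreseeable volunteer. For her, a rule that looks only at the goal points the wrong way.

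What is at stake is the safety of the individual woman. The article's Introduction itself describes energy-restricted diets as favouring dysfunctional eating and links them to eating disorders. By the sponsor's own account, a deficit should not be handed out without regard to who receives it.

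**Working it through.** The article states no figure on this point, so the check sets the rules side by side and follows one hypothetical participant through them.

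1. **Can she enter?** Take a woman aged 25 to 50, dissatisfied with her body, with a phone and free to attend, with none of the listed diagnoses or conditions, and underweight. She meets every inclusion criterion. No exclusion applies, because underweight is not listed and the eating-disorder exclusion requires a diagnosis.
2. **What does the rule give her?** If she is allocated to diet and wishes to lose weight, the Interventions section gives her the calculated requirement minus 300 kcal. If she wishes to gain weight, she receives a surplus of 300 to 500 kcal, and there is no problem. The gap therefore concerns only underweight diet-arm women who wish to lose weight.
3. **Does another provision stop it?**

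| Provision | What it governs | Makes the deficit conditional on weight status? |
|---|---|---|
| Exclusion of eating disorders | Diagnosed cases only | No |
| Weight and height at meeting 1 | Measured, but no rule uses them to withhold a deficit | No |
| Nutritional adjustments | Fibre, macronutrients and micronutrients | No |
| Week-5 consultation | General review about four weeks after meeting 1, without a weight criterion | No |
| Weekly adverse-event conversations (Ethical aspects) | Detection and referral after an event | No |

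4. **What would a limit mean in practice?** The article gives no limit. Taking a BMI of 18.5 kg/m² as an example, the corresponding weight is 18.5 × height²:
 - 1.50 m: 18.5 × 2.25 = 41.6 kg
 - 1.60 m: 18.5 × 2.56 = 47.4 kg
 - 1.70 m: 18.5 × 2.89 = 53.5 kg

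 The heights are assumed for illustration. The limit can be applied with the two measurements already taken at meeting 1.
5. **How many women?** The article gives no weight distribution for the volunteers, so no frequency can be derived. One such woman would be 1/38 = 2.6% of the planned diet arm.

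**The case against.** The strongest reply is that this is one summary sentence in a condensed article. A nutritionist calculates each plan, with the Estimated Energy Requirement only as a reference. The sentence is visibly incomplete, since it gives no energy value for a woman who wants to keep her weight, so some professional judgement is already assumed. Contraindications to a deficit could stand in the full protocol or an intervention manual. Weight and height are taken at the same meeting as the history used to build the plan, so the nutritionist would have the facts at hand.

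Much of this stands, and it lowers the severity. It does not remove the point. The article does more than stay silent: it names the deciding criterion, the woman's goal, and it gives the eligibility criteria. Together they admit the case. A nutritionist who withholds the deficit acts sensibly, but without support from the written rule.

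A second objection is that the proposed exception changes the woman's calories but not the message of the meetings, because meeting 2 is about motivation for weight loss. That is true. The exception removes the prescribed deficit and claims no more.

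**Conclusion.** The point holds as a low-severity safety correction. Under the rule as written, an underweight woman without a diagnosed eating disorder who wishes to lose weight would be prescribed a 300 kcal deficit. Nutritionist judgement and the week-5 review make this less likely but do not bar it. The number affected is unknown and may be zero. The conclusion rests on reading the goal-based sentence as the operative rule, with no exception elsewhere in the article.

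Two stronger readings are tempting, and the article supports neither.

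- **Lost data.** A reader might infer that withholding the deficit would cost the woman her data, because Data management says "To those who discontinue or deviate from the intervention protocol, all data exclusion will be necessary". That sentence most naturally concerns participants who leave or depart from the intervention, not a nutritionist's clinical decision. The Interventions section also expressly allows the plan to be adjusted in week 5.
- **Quantified harm.** A reader might multiply the deficit over the weeks of the programme and present the total as harm. The article does not state that the 300 kcal is per day, does not say when the plan is handed over, and links no energy total to a clinical consequence.

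**What to change.** Add to the Interventions section, directly after the deficit and surplus rule:

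> No energy deficit is prescribed to a participant who is underweight by the weight and height measured at meeting 1 (for example BMI below 18.5 kg/m², limit to be confirmed by the clinical team), whatever her goal. She stays in her allocated group on a plan without a deficit, and this counts as following the protocol.

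The surplus for underweight women who wish to gain weight stays as it is. Eligibility need not change, since the diet rule already provides for women who wish to gain.

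The cost is small: one short addition, communicated to the Ethics Committee as the Ethical aspects section provides for protocol changes. No new measurement is needed, and sample size, allocation and meeting content do not change. The downside is that any such woman receives a diet plan without a deficit, which slightly weakens the contrast between the arms.
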